# Compliance with, Deviation from, Changes in, or Amendment to the Protocol

## Compliance with the Protocol

The principal investigator and the subinvestigator shall abide by this protocol in implementing the clinical trial.

## Protocol Deviations or Changes

The principal investigator and subinvestigators shall not deviate from or make any changes to the protocol without prior written approval by the Institutional Review Board after consultation, unless there is an imminent danger to a subject that has to be avoided or any other situation medically justifiable, or a change related solely to administrative matters is involved.

If the principal investigator deviates from the protocol on grounds of avoidance of imminent danger to a subject or other medically justifiable situation, the principal investigator will describe the justification and relevant matters in a report concerning deviation from the protocol for avoiding an imminent danger. The report will be submitted to the head of the institution, and a copy of the report will be kept by the principal investigator. The principal investigator and subinvestigators will record all deviations from the protocol, regardless of the cause. The subject or his/her legally acceptable representative may refuse to participate or may withdraw from the clinical trial at any time. The subject’s refusal or withdrawal will not result in penalty or loss of benefits to which the subject is otherwise entitled.

# Statistical Analyses

## Populations for Analyses

### Analysis Sets

[Safety]

The safety analysis set will include a set of subjects to whom the investigational products had been administered at least once.

[Efficacy]

1) Full Analysis Set (FAS)

The full analysis set (FAS) will be based on the intention-to-treat (ITT) principle, and will include all patients in this trial other than those who fall under any of the following conditions:

・Violation of eligibility criteria (patients who do not meet main registration criteria for this trial)

・Patients in whom the investigational products had never been administered

・Non-existence of baseline nor treatment data

・Withdrawal of consent during the trial and refusal to allow use of all data

2) Per Protocol Set (PPS)

The Per Protocol Set will include a set of subjects who meet the eligibility criteria for the efficacy analysis based on the standards for subject analysis sets developed before database locking. Eligibility criteria for data to be measured chronologically shall be specified for individual points in time for measurement.

The main analysis set for efficacy in this trial is to be the FAS. For main efficacy endpoints, statistical analysis of the PPS will also be performed. Comparison of the results of two distinctive analysis sets will be used to evaluate the robustness of main analysis results of the trial.

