# Investigational Products

## Brief Description of the Investigational Products

1) Test drug

(1) Product name: NPC-12T active substance tablets

(2) Ingredients: Sirolimus

(3) Dosage form: White, sugar-coated tablets containing sirolimus 1 mg each

(4) Storage: Stored in airtight containers, at ambient temperature, and away from light.

2) Comparator

(1) Product name: NPC-12T placebo tablets

(2) Dosage form: Tablets containing excipients identical to those of the active substance NPC-12T, but not containing sirolimus

(3) Storage: Stored in airtight containers, at ambient temperature, and away from light.

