# Procedures of the Trial

## Registration of Patients

The principal investigator or subinvestigator will obtain written informed consent from patients who are thought to satisfy the inclusion criteria, or their legally acceptable representatives, and register the patients in accordance with the following procedures:

| 1) Selection of patients | |
| --- | --- |
|  | The principal investigator or subinvestigator will carefully examine whether respective patients are eligible to participate in the clinical trial, taking account of patients’ health conditions, symptoms, age, gender, relationship with the principal investigator, and participation in any other clinical trials. |
| 2) Informed consent | |
|  | The principal investigator or subinvestigator will provide information pertinent to the clinical trial to patients who are thought to satisfy the inclusion criteria of the trial, and obtain written informed consent from the patients or their legally acceptable representatives. |
| 3) Assignment of subject identification code | |
|  | Subsequent to informed consent, required data will be entered into the electronic case report forms, and subject identification code numbers will be assigned. This will be recorded on the subject screening list. The code numbers will be used for identification of the patients throughout this trial. |
| 4) Screening | |
|  | Patients will go through screening two weeks (+/- seven days) before the initial intake of the investigational products. |
| 5) Confirmation of eligibility by the principal investigator or subinvestigator | |
|  | Prior to starting the first dose of the investigational products, the principal investigator or subinvestigator will judge whether patients satisfy the inclusion criteria, based on the assessment during the screening phase, using the eligibility check sheet. |
| 6) Registration of subjects and assignment of investigational products (V1) | |
|  | Patients whose eligibility to participate in the trial is confirmed in 5) will be registered and have investigational products assigned via the electronic case report form. Unique code numbers (pharmaceutical agent numbers) will be assigned to the registered subjects. This will be recorded in the subject screening log.  Patients whose eligibility is denied in 5) will be treated as screen failures. Screen failures will be recorded in the remarks column of the subject screening log. |

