# Administration of Investigational Products

Figure 1 Dosing Protocol

Phase I (single-blind): NPC-12T placebo tablets for 3 months (12 weeks)

Phase II (double-blind): NPC-12T active substance tablets or NPC-12T placebo tablets for 6 months (24 weeks)

[Dosage at the outset of the trial]

Subjects weighing less than 40 kg will take one 1-mg tablet orally once every other day.

Subjects weighing 40 kg or more will take one 1-mg tablet orally once per day.

The investigational products are to be taken before sleep.

The bodyweight measured at V1 will be referred to in determining dosage throughout the trial.

<Rationale for the dosing time>

The package insert of Rapamune 1 mg tablets was referred to when setting the dosing time. The insert cites reports that state administration of the tablet after a high-fat meal increased the blood concentration of sirolimus. To reduce effects of high-fat meals, the dosing time of the investigational products is set to be before sleep.

[Prescription of the investigational products]

In Phase I (V1, V2, V3, and V4) and Phase II (V5 and V6), the principal investigator or subinvestigator will prescribe investigational products in accordance with the dosage at the start of the trial described above.

In Phase II (V7, V8, V9, V10, and V11), the unblinded doctor will instruct the principal investigator and subinvestigators on the prescription of the investigational product based on the criteria for dosage change. The principal investigator or subinvestigator will make a judgment on whether dosage reduction is required or dosage increase is permissible, taking account of subjects’ safety, including risks of adverse events. If the conditions are deemed appropriate, the principal investigator or subinvestigator will prescribe the investigational products as instructed by the unblinded doctor. The unblinded doctor will provide instructions to the principal investigator or subinvestigator in accordance with the trough concentration measurements and the prescription schedule generated by the randomization manager. The trough concentration measurements and the prescription schedule are not to be disclosed to any person except the unblinded CRCs until the end of the trial, and will be kept securely locked in a cabinet accessible only to the unblinded doctor.

[Criteria for dosage change]

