## Adverse Events

### Definition of Adverse Events

An adverse event in this trial refers to any untoward medical occurrence in a subject from initial administration of investigational products (V1) to follow-up observations (V13). The event may not necessarily have to have a causal relationship with administration of investigational products in this trial. An adverse event can therefore be any unfavorable and unintended sign (including an abnormal laboratory finding, for example), symptom, or disease temporally associated with the use of a medicinal product, whether considered related to the medicinal product or not.

Exacerbation of the primary disease, including episodes, will not be regarded as an adverse event, with the exception of cases in which causal relationship with the investigational products cannot be ruled out.

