### Assessment of Adverse Events

The items listed below will be examined and recorded on the electronic case report forms with regard to adverse events that occur from the initial administration of investigational products (V1) to follow-up observations (V13).

If a diagnosis is settled based on signs or symptoms, the diagnosis rather than the signs or symptoms should be recorded. With regard to vital signs and clinical test measurements, changes from conditions before administration of investigational products should be assessed to determine whether the changes are clinically significant. An abnormal change that is considered clinically significant is to be counted as an adverse event. An abnormal change that is relevant to symptoms and signs already recognized as an adverse event, shall not be required to be newly reported as a separate adverse event.

・Name of the adverse event

・Date of occurrence

・Severity

・Seriousness

・Actions taken (administration of investigational products or other actions)

・Outcome and date of outcome confirmation

・Causal relationship with the investigational products

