## Statistical Analysis of Safety

### Adverse Events

The number of occurrences and types of adverse events and of side effects will be sorted by clinical symptoms and by abnormal change of clinical test results. A two-sided 95% confidence interval of the incidence rate by respective dosing arms will be calculated using the Clopper-Pearson method.

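### The by-arm adverse event incidence has no split at V5, so on the natural reading the sirolimus arm's rate includes 12 weeks of placebo run-in and any subject who never took sirolimus

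*Protocol*

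**What the plan says.** All of the following is in the protocol.

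- **Safety set (17.1.1):** "The safety analysis set will include a set of subjects to whom the investigational products had been administered at least once".
- **What counts as a product (Brief Description of the Investigational Products):** the comparator is listed alongside the test drug, as "Product name: NPC-12T placebo tablets".
- **When arms are assigned (Registration of Patients):** at V1, under the step "Registration of subjects and assignment of investigational products (V1").
- **What is taken when (Administration of Investigational Products):** "Phase I (single-blind): NPC-12T placebo tablets for 3 months (12 weeks"), then "Phase II (double-blind): NPC-12T active substance tablets or NPC-12T placebo tablets for 6 months (24 weeks").
- **Adverse event window (14.10.1):** "any untoward medical occurrence in a subject from initial administration of investigational products (V1) to follow-up observations (V13"). Section 14.10.2 uses the same window for recording.
- **Analysis (17.4.1):** "A two-sided 95% confidence interval of the incidence rate by respective dosing arms will be calculated using the Clopper-Pearson method".

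Adverse events and side effects head the primary endpoints. Section 17.1.2 leaves standards for analysis sets to be settled before database lock, and 17.9 promises a statistical analysis plan before unblinding.

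**The concern.** Each rule is ordinary on its own; the difficulty comes from combining them in a trial with a placebo run-in after assignment. A single run-in placebo tablet is enough to enter the safety set. A subject assigned to sirolimus at V1 belongs to that arm for 12 weeks before any sirolimus can be taken. If incidence is then computed by arm over the defined window, two separate errors enter the sirolimus figure:

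- **Numerator:** events with onset during the run-in are counted as events of the sirolimus arm.
- **Denominator:** a subject who leaves before V5 remains among the sirolimus subjects without having been exposed.

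The figure affected is the primary safety result. With 12 subjects planned for that arm, one misplaced subject moves the incidence by 1/12, or 8.3 percentage points. The protocol does separate the phases for efficacy: several secondary endpoints compare the end of Phase I with the end of Phase II. It draws no such line for safety.

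**Working it through.** **Inputs from the protocol.** V1 is day 1, V5 is week 12, V12 is week 36 and V13 is week 40 (Table 1). Planned allocation is 12 active and 4 placebo (17.5). No background event rate and no run-in dropout rate are given, so both are assumed below and shown over a range.

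**The plan's own safety figure.** Section 17.5 claims 85% for detecting an event of 15% incidence. The chance of at least one case among n subjects is 1 − 0.85^n. For n = 12 this is 0.858, which matches; for n = 16 it is 0.926, which does not. The figure is right for the 12 active-arm subjects and is not in dispute.

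**Share of observed time on placebo in the sirolimus arm.** 12/40 = 30% of the V1 to V13 window, or 12/36 = 33% of the dosing weeks.

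**Numerator, constant hazard assumed.** Let p be the incidence over V5 to V13 (40 − 12 = 28 weeks) with no drug effect. Then h = −ln(1 − p)/28 per week, and the incidence over V1 to V13 is 1 − exp(−40h).

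| Incidence over V5–V13 | Same hazard over V1–V13 |
| --- | --- |
| 15% | 20.7% |
| 30% | 39.9% |
| 50% | 62.9% |

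For the first row, h = 0.1625/28 = 0.00580, 40h = 0.232, and 1 − exp(−0.232) = 0.207.

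**Numerator, run-in incidence assumed directly.** Take 15% in Phase II and an independent run-in incidence b. The combined incidence is 1 − 0.85(1 − b), and the chance that at least one of 12 subjects has a run-in event is 1 − (1 − b)^12.

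| Run-in incidence b | Incidence over V1–V13 | At least one run-in event among 12 |
| --- | --- | --- |
| 5% | 19.3% | 46% |
| 10% | 23.5% | 72% |
| 20% | 32.0% | 93% |
| 30% | 40.5% | 99% |

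**Denominator.** If k of 12 subjects leave before V5 and stay in the denominator, a true 15% reads as 0.15 × (12 − k)/12. This is 13.8%, 12.5% and 11.3% for k = 1, 2 and 3. The effect is zero if nobody leaves in the run-in.

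The two errors act in opposite directions and have unrelated causes, so they cannot be relied on to cancel.

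**The case against.** The strongest reply is that the protocol never states the analysis being criticised. Section 17.4.1 speaks of dosing arms, gives no time window, and does not say whether arms are as randomised or as treated. The V1 to V13 window sits in Section 14, where it governs what is an adverse event and what is recorded; collecting from the first tablet is correct. By-phase tables are common content for a statistical analysis plan, and that plan is not at hand.

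Part of this stands. Counting by randomised arm from V1 is an inference, though the natural one: arms are assigned at V1, no other window appears, and there is no as-treated rule. The deferral argument is weaker. The protocol has already fixed the one-dose rule, the V1 start and a per-arm rate. Section 17.1.2 defers standards for analysis sets, not the event window.

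The size is also modest against the precision available. Moving from 15% to 20.7% is 1.8 against 2.5 expected subjects out of 12, while the Clopper-Pearson interval is about 2% to 48% for 2/12 and 5% to 57% for 3/12.

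Three stronger readings are tempting, and the documents do not support them:

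- **That laboratory and vital-sign changes are analysed against pre-V1 values.** Section 14.10.2 does say that "changes from conditions before administration of investigational products should be assessed to determine whether the changes are clinically significant", but this tells the investigator when an abnormal value becomes an adverse event. The analysis is in 17.4.2, which does not define baseline.
- **That the stated 85% detection probability is undermined.** With 11 or 10 exposed subjects it would be 0.833 or 0.803, but dropout causes that fall, and it is the same under any safety-set definition.
- **That a between-arm risk ratio is pulled toward one.** Section 17.4.1 plans only within-arm intervals, with no between-arm contrast for adverse events.

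**Conclusion.** The concern holds, limited to the adverse event incidence and its intervals in 17.4.1. Followed on their natural reading, the stated rules count events from 12 of 40 weeks of placebo time in the sirolimus arm and keep never-exposed subjects in its denominator. The illustrative size is a rise from 15% to about 21% if the background hazard is constant. Run-in incidences of 5% to 30% would turn 15% into 19% to 41%. The inflation needs only one run-in event in a subject with no later event; the dilution needs a withdrawal before V5, for which the protocol gives no rate. The net direction is therefore not known in advance.

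This should be fixed rather than must be fixed. Onset dates are recorded for every event, so the right tables can be produced from data already planned. Randomisation, dosing and data collection are untouched. A statistical analysis plan may already contain a phase split; even so, the protocol's wording should agree with it.

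**What to change.** Amend the wording of 17.1.1 and 17.4.1:

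1. Base the by-arm adverse event and side effect incidence, with the Clopper-Pearson intervals, on subjects with at least one Phase II dose, classed by the Phase II treatment received.
2. In those rates, count events with onset from the first Phase II dose to V13.
3. Report Phase I events separately, pooled over all dosed subjects and labelled as placebo run-in. Subjects who leave before V5 then still appear in the safety report.
4. Keep collection from V1 and leave 14.10.2 unchanged.

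The cost is a few sentences, matched in the statistical analysis plan before unblinding. No new data, visits or subjects are needed.

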### Data Handling

Standards for analysis sets will be established before database lock.

## Demographic Variables and Baseline

Summary statistics of the subjects’ basic data (e.g., gender, age, and weight) and baseline will be calculated for each dosage arm.

## Statistical Analysis of Efficacy

Assessment of efficacy in this trial is regarded as a secondary objective. With regard to continuous endpoints, summary statistics of changes or percentage changes based on actual measurements and from baseline at each point in time will be calculated for each dosage arm. A one-sample *t*-test will be used for comparison between actual measurements and baseline values at each point in time for each dosage arm. The two-sided 95% confidence interval for average change for each dosage arm will then be estimated. Using a two-sample *t*-test, the change or percent change at each point in time between the two arms will be compared. The two-sided 95% confidence interval for average difference between the two arms will be estimated. If the data is found to be non-normal, use of nonparametric methods and statistical methods based on probability distribution other than normal distribution will be considered. With regard to binary endpoints, a contingency table will be compiled for each point in time, and Fisher’s exact test will be applied in making comparison of the distribution in the two dosage arms. The Clopper-Pearson method will be applied to estimate the two-sided 95% confidence interval for each dosage arm. The difference in the two-sided 95% confidence interval will be estimated using the normal approximation.

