## Target Study Sample Size

A sample size of 16 subjects is expected to be studied: 12 subjects for NPC-12T active substance arm, and 4 subjects for NPC-12T placebo arm.

[Reason for choice of sample size]

As this clinical trial will focus on a rare disease, and is exploratory, feasibility was the main aspect that was considered in setting the sample size. In terms of safety analysis, provided that clinically significant adverse events exist, the size is sufficient to detect adverse events of 15% incidence with 85% accuracy. In terms of efficacy analysis, when making a comparison of NPC-12T arms concerning hearing test endpoints of periods without treatment and with treatment, a difference can be detected at 80% power (two-sided 5% significance level), if the number of evaluable subjects is 11 and Cohen’s d for endpoints is 0.85.

In estimation of correlation coefficient between evaluation indices, if data of two arms are integrated for evaluation, and the number of evaluable subjects having population correlation coefficient of 0.7 (i.e., medium to high degree of correlation) is 13, then a difference can be detected at a minimum of 80% power (two-sided 5% significance level).

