## Significance Level and Multiplicity

The level of significance used for all analyses in this trial is to be two-sided 5%. The confidence coefficient of confidence interval is to be two-sided 95%. As the efficacy analysis in this trial is for a secondary purpose, multiplicity of different endpoints and time points will not be adjusted.

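### The efficacy power figure is for an untreated-period v treated-period contrast, but section 17.3 tests repeatedly measured continuous endpoints visit by visit and never writes that contrast as a test

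*Protocol*

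**What the plan says.** **Power statement.** Protocol section 17.5 (Target Study Sample Size) makes its efficacy case "concerning hearing test endpoints of periods without treatment and with treatment, a difference can be detected at 80% power", with 11 evaluable subjects and the condition that "Cohen’s d for endpoints is 0.85". The synopsis places this comparison in the active arm. The same paragraph says feasibility was the main consideration, and adds a safety argument (15% incidence) and a correlation argument (0.7 with 13 subjects).

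**Tests.** For continuous endpoints, section 17.3 (Statistical Analysis of Efficacy) prescribes a one-sample t-test that "will be used for comparison between actual measurements and baseline values at each point in time for each dosage arm", then a two-sample t-test of the change between arms at each time point. It does not say what baseline means for these tests.

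**Error rate.** Section 17.6 sets two-sided 5% for all analyses and states that "multiplicity of different endpoints and time points will not be adjusted", because efficacy is a secondary purpose.

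**Robustness check.** Section 17.1.1 (Analysis Sets) adds: "For main efficacy endpoints, statistical analysis of the PPS will also be performed". The list in section 17.3.1 does not rank the nine secondary endpoints.

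**Visits.** Section 14.7.5 schedules pure-tone audiometry at V1, V3, V4 and V5, then at V7 to V12 (six treated visits), and at V13. Section 14.5 has the Dizziness Handicap Inventory completed at every visit.

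**The concern.** The protocol attaches a power figure to one kind of comparison and then prescribes another for endpoints read at several visits. In a disease whose hearing fluctuates, one reading minus a baseline reading is noisier than a difference of two period means. If the power figure belongs to the period comparison, it does not carry over to the visit tests.

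The visit tests also give one endpoint several chances at 5%. In a 16-subject trial meant to inform later protocols, an isolated visit with p < 0.05 could be read as the efficacy signal, while the more precise comparison, available from the same data, is not laid down as a test.

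**Working it through.** **1. The plan's own figure.** Inputs from section 17.5: d = 0.85, two-sided 5%, 80% power, n = 11.

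- Normal approximation for a paired contrast: n = ((1.960 + 0.842)/0.85)² = 10.86, rounded up to 11. Power at 11 = Φ(0.85·√11 − 1.960) = 80.5%. The figure is reproduced.
- Exact noncentral t (the test family named in 17.3), 10 df, noncentrality 0.85·√11: 72.0%. The gap from 80% to 72% is the approximation and is a separate matter. 72% is the right comparator below, because every test here is a t-test.

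**2. Power of a single-visit test.** Assumptions, none given in the protocol:

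- d = 0.85 refers to the Phase II mean minus the Phase I mean;
- Phase I readings are V1, V3, V4 and V5 (V5 counted as untreated, since Phase II product is first prescribed there), and Phase II readings are V7 to V12, all 4 weeks apart;
- unit-variance fluctuation within subject, AR(1) correlation ρ per 4 weeks from 0 to 0.7;
- the same drug effect at every treated visit.

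The mean effect is then the same in each contrast, so d for a visit test = 0.85 × SD(period contrast)/SD(visit contrast). At ρ = 0:

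- period contrast: √(1/4 + 1/6) = 0.645
- V12 − V5: √2 = 1.414, so d = 0.85 × 0.645/1.414 = 0.39
- V12 − Phase I mean: √(1 + 1/4) = 1.118, so d = 0.85 × 0.645/1.118 = 0.49

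For other ρ, each SD is √(c′Rc), with c the contrast weights and R the AR(1) matrix. Power is noncentral t at n = 11.

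| ρ | SD period | SD V12−V5 | d | power | SD V12−Phase I mean | d | power |
|---|---|---|---|---|---|---|---|
| 0 | 0.645 | 1.414 | 0.39 | 21% | 1.118 | 0.49 | 31% |
| 0.3 | 0.783 | 1.414 | 0.47 | 29% | 1.178 | 0.57 | 40% |
| 0.5 | 0.867 | 1.403 | 0.53 | 35% | 1.225 | 0.60 | 44% |
| 0.7 | 0.898 | 1.328 | 0.57 | 41% | 1.236 | 0.62 | 46% |

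If subjects also differ in drug effect, the loss shrinks. With an effect SD of 1 fluctuation SD at ρ = 0.7, the SD ratio for V12 − V5 is √(0.898² + 1)/√(1.328² + 1) = 1.344/1.663 = 0.81, d = 0.69 and power is about 54%, still below 72%.

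**3. False positives with no drug effect.** One endpoint, six treated visits, each compared with V5; 12 active and 4 placebo subjects; simulated t-tests at 5%. Six independent tests would give 1 − 0.95⁶ = 26.5%. The shared baseline and serial correlation lower this:

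| ρ | at least one p < 0.05, active arm | counting between-arm tests too |
|---|---|---|
| 0 | 22% | 35% |
| 0.3 | 21% | 34% |
| 0.5 | 20% | 32% |
| 0.7 | 19% | 31% |

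Allowing for simulation error, the ranges are about 19–22% and 30–35%. Taking the Phase I mean as baseline does not lower them.

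**4. Which endpoints are affected.** Endpoints 1 and 3 are yearly rates; 2, 4 and 7 are episode maxima or durations. All five give one value per period by nature. Endpoints 5 and 9 are percentages that compare the end of Phase I with the end of Phase II. Endpoint 8 is a Phase I to Phase II change, though how each phase's Dizziness Handicap Inventory scores are summarised is not stated. That leaves endpoint 6, threshold during remission, as the clear case, and endpoint 8 as a possible one.

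**The case against.** The strongest reply is that the power loss rests on a mapping the protocol does not make. Section 17.5 attaches d = 0.85 to endpoints without saying how readings are combined, and section 17.3 nowhere fixes baseline as one V5 reading. Endpoint 6 concerns remission, which leaves out the episodes that supply much of the fluctuation. Nightly home audiometry and the five-reading baseline used for episode detection could also make a visit comparison less noisy. This stands as a limit on the size: 21–41% and 31–46% are conditional figures. It does not remove the mismatch, because no reading of section 17.3 supplies the untreated v treated period test for a repeatedly measured continuous endpoint.

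It can also be said that baseline definitions and the choice of main endpoints belong in the SAP, which section 17.9 promises before unblinding. That holds for naming the endpoints. It does not hold for the contrast, since the protocol itself states both the powered comparison and a different set of tests.

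Stronger readings that the documents do not support:

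- *The whole sample size rests on this contrast.* It does not: feasibility comes first, with safety and correlation arguments besides.
- *The period comparison is absent throughout.* Most secondary endpoints are period-level or already compare the phases.
- *Declining multiplicity adjustment is an error.* It is declared, and defensible for secondary efficacy in an exploratory trial.
- *An inert drug will probably give a significant result.* For one endpoint the risk is raised but below one half. Figures above one half appear only when several endpoints, visits and both test types are counted together, and how many endpoints are tested visit by visit is itself an assumption.
- *One main endpoint must be imposed.* The trial aims to explore which tests evaluate hearing best, so that choice is arguable.

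**Conclusion.** The concern holds in a limited form. For continuous endpoints measured repeatedly, chiefly endpoint 6, the tests in section 17.3 are not the comparison for which section 17.5 states power. On the assumptions above, a single-visit test has roughly one-third to two-thirds of the power of the period contrast (21–46% against 72%), and the six visits together carry about four times the nominal 5% false-positive risk in the active arm. The direction is secure as long as visit readings fluctuate and the drug effect is reasonably steady over Phase II. The size depends on correlations and on a meaning of d that the protocol does not give. This does not touch the primary safety objective. It is worth correcting because the more precise test uses data already collected.

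**What to change.** **Section 17.3.** For each repeatedly measured continuous endpoint, make the main efficacy contrast the within-subject Phase II on-treatment mean minus the Phase I mean; for rate endpoints, the Phase II minus the Phase I annualised rate. Test it once within the active arm and once between arms. State which visits count as Phase I, and that V5 is untreated. Keep all per-visit results as estimates with 95% intervals and nominal p-values.

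**Section 17.1.1.** Apply the FAS v PPS comparison to this contrast. Which endpoints are the main ones may be set in the SAP before unblinding.

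**Section 17.6** can keep its position on multiplicity.

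**Cost.** Wording only; no added subjects, visits or measurements. An effect confined to late visits is diluted in the period mean, and because dose may change from V7 to V11 that mean pools different exposures; the per-visit estimates still show both. The between-arm test with 12 v 4 subjects has only about 28% power at d = 0.85 (14 df, noncentrality 0.85·√3), so its interval will say more than its p-value.
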